**Abstract**

| item | Contents |
| --- | --- |
| Purpose | To investigate the effectiveness of mindfulness meditation for trait impulsivity in patients with Parkinson's disease (PD). |
| Research subjects | Patients with PD. |
| Inclusion criteria | 1. Clinically established or probable PD diagnosed by MDS clinical diagnostic criteria for Parkinson's disease.  2. 20 years or older.  3. Patients providing informed consent. |
| Exclusion criteria | 1. Severe dementia or hallucination/delusion.  2. Severe hearing loss or severe visual impairment.  3. Disturbance in consciousness.  4. Participating in other intervention trials.  5. Change in antiparkinsonian drugs within 28 days before enrollment.  6. New antipsychotics or antidepressants within 84 days before enrollment.  7. Symptomatic stroke or encephalitis within 84 days before enrollment.  8. Daily meditation or yoga. |
| Informed consent | Prior to the start of the study, the investigating doctor explains it to the participant in an easy-to-understand manner using the explanation document and consent form. The participant is given sufficient time to think and is confirmed to have understood the contents of the test well. The consent form requires the date of consent and signatures from the investigating doctor who gave the explanation and from the participant who gave consent after the explanation. A copy of the consent form is then given to the participant and the original is retained. |
| Intervention method | Mindfulness meditation.  Participants undergo a weekly group session for approximately 30 min of mindfulness meditation for 8 weeks, and are required to practice meditation daily for 15 min on 6 or 7 days per week. Mindfulness meditation includes body scans, mindfulness movements, and controlled breathing. The participants are given instruction papers in each group session for daily home-based practice, and complete an implementation record. In addition to regular meditation, participants also receive instructions on meditation techniques during daily activities, such as eating meditation and walking meditation. During the period from registration to the final evaluation, the antiparkinsonian, antipsychotic, or antidepressant drugs used by participants are not permitted to be changed. |
| Research method  (Treatment schedule, etc. ) | We recruit patients with PD visiting our institute, explain the purpose and methods of this trial, and request research participation. Participants are registered after providing written informed consent. After registration, they are evaluated by cognitive test (MMSE), motor symptom evaluation (UPDRS part 3, Hoehn- Yahr), MRI, questionnaire evaluations (BIS-11, QUIP-RS-J, HADS, PDQ-8, MAAS, NPI-Q). For cases with wear-off phenomenon, MMSE, UPDRS, and MRI should be performed in “ON” state. MRI can be skipped in difficult cases, such as for patients with claustrophobia.  Group sessions of mindfulness meditation are performed once a week under the guidance of a professional clinical psychologist, including approximately 30 minutes of guidance and 15 minutes of mindfulness meditation. Mindfulness meditation includes body scans and controlled breathing. Participants are required to practice meditation daily for 15 minutes on 6 or 7 days per week. The participants receive instruction papers in each group session for daily home-based practice and complete an implementation record. Clinical evaluations are performed in week 2 and week 8, and MRI is conducted within 14 days after week 8 evaluation. Daily mindfulness meditation continues until the final MRI. For evaluation items and schedule, refer to “#9, Inspection items and schedule." |
| Concomitant prohibited drugs | From the date of registration to the end of study, new additions and changes to antiparkinsonian drugs, antipsychotic drugs, and antidepressants are prohibited. |
| Outline of observation / inspection schedule | - Demographics: age, gender, height, weight, medical history (duration, age at onset, etc.), medication, past history and complications, and cognitive function (MMSE). - Motor symptoms: MDS-UPDRS, Hoehn-Yahr scale. - Questionnaires: Impulsivity Evaluation Scale (BIS-11), Impulse Control Disorder Scale (QUIP-RS-J), Depression and Apathy Evaluation Scale (HADS), QOL Evaluation Scale (PDQ-8), Mindfulness Evaluation Scale (MAAS) is performed after the observation period, at 2 weeks and at 8 weeks. If there are any caregivers, NPI- Q is also performed as an evaluation of psychiatric symptoms. - MRI is performed twice, before the intervention and then within 14 days after the end of the study. - Evaluation of achievement rate of mindfulness meditation using implementation record (15 minutes, 6 or 7 days per week) |
| Primary outcome | BIS-11 (Barratt Impulsiveness Scale) score reduction following 8 weeks of mindfulness meditation. |
| Target number of cases | 20 |
| Subject registration period | Approval date - 08/31/2021 |
| Research period | Approval date – 08/31/2024 |

**1. Research purpose and significance**

**1-1. Purpose**

We aim to investigate the effectiveness of mindfulness meditation for trait impulsivity in patients with Parkinson's disease (PD).

**1-2. Significance**

This clinical study provides data on whether mindfulness meditation can control the impulsivity of PD. In addition, it will be the preliminary data for phase III clinical trials.

**2. Background**

PD is the second most common neurodegenerative disease after Alzheimer's disease, affecting 100~150/100,000 people. PD is caused by degeneration of dopaminergic neurons and presents as motor symptoms, such as akinesia, tremors, and rigidity. No radical cure has yet been developed; the main treatment is dopamine replacement therapy, such as levodopa or dopamine agonists, which is also described in clinical practice guidelines. Conversely, it has been suggested that motor symptoms are only one aspect of PD, and non-motor symptoms have also been highlighted. Psychiatric symptoms, such as depression, apathy, anhedonia, and impulse control disorders (ICDs), are major problems that can reduce quality of life. ICDs have been reported to occur in about 13% of PD patients, and include pathological gambling, binge eating, excessive shopping and hypersexuality. The ICD related symptoms include punding and dopamine dysregulation syndrome. To improve ICDs, dopamine replacement therapy needs to be reduced. Meanwhile, dose reduction of dopamine agonist can induce dopamine agonist withdrawal syndrome (DAWS).

The pathophysiological mechanism of ICDs in PD has not been elucidated. In PD, the dopaminergic neurons in the substantia nigra pars compacta are reduced, but the dopaminergic neuron in the ventral tegmental area, which plays an important role in reward and goal-directed behavior, are relatively preserved. Dopamine replacement therapy has been reported to cause ICDs due to hyperexcitability from the ventral tegmental area to the ventral striatum and frontal lobe. Owing to individual differences in the likelihood of developing ICDs, some vulnerabilities in the reward system have been shown in patients with ICD. In addition, patients with high impulsivity have more severe ICDs. The trait impulsivity itself may therefore be a psychological symptom of PD.

In recent years, mindfulness meditation has attracted attention as a non-pharmacotherapy in the field of psychiatry. The mindfulness-based stress reduction (MBSR) developed by Jon Kabat-Zinn et al. is an eight-week secular course of practice derived from Buddhist meditations methods. Based on MBSR, a short version (15 minutes) and MBCT have been developed. These methods have been shown to improve depression and anxiety, and also prevent the recurrence of depression. There have been recent reports of improved symptoms of attention deficit hyperactivity disorder, drug abuse and decreased impulsivity in adolescents. On the other hand, in a phase III trial, the effect of mindfulness yoga on depression has been shown in patients with PD. In this context, mindfulness meditation is thus a promising candidate treatment for ICDs or controlling impulsivity. Its effectiveness has not been fully investigated, however, so we planned a single-arm intervention study as a pilot study to investigate whether the impulsivity of PD is improved by mindfulness meditation.

Furthermore, to investigate the pathophysiology of impulsivity and changes of brain function by mindfulness meditation, we also evaluate structural and functional MRI. Recent developments in resting-state functional MRI (rs-fMRI) analysis have made it possible to non-invasively measure functional connectivity of the brain. There have been various reports related to mindfulness, impulsivity, and rs-fMRI: the association between default mode network (DMN) and impulsivity, the association between mindfulness scale (MAAS) and attention network, or inter-large-scale networks; suppressing effect of DMN hyperexcitability by meditation. The functional connectivity between the striatum and the motor system is reduced in patients with PD, which can be improved by dopamine replacement therapy. Regarding ICDs, dysfunction in the ventral striatum, which controls the reward system, has been reported, although with some controversy. Some reports suggest hypoactivation, while others suggest hyperactivation. Furthermore, one report suggests a decreased functional connectivity between association striatum and inferior temporal cortex. In other words, there may be a wide range of dysfunctions beyond the reward system. In addition to dysfunction, MBSR has also been reported to increase gray matter volume in the amygdala and hippocampus in patients with PD. Based on the results of previous studies, as a secondary exploratory outcome we will conduct rs-fMRI and structural MRI before and after mindfulness meditation for PD.

**3. Research plan**

**3-1. Study population**

The target is patients with Parkinson's disease who visit our department.

**3-2. Design**

(1) Type of test

Single-center, single-arm, open-label, pilot study

(2) Intervention

Mindfulness meditation

(3) Explanation of test design

This pilot study aims to explore the effectiveness of mindfulness meditation for impulsivity of PD.

**3-3. Study period**

Study period: 2019/9/1- 2024/8/31 (5 years)

Registration period: 2019/9/1-2021/8/31

**3-4. Target registration number**

The target number is 20 patients with PD.

**3-5. Mindfulness meditation and measurement of outcomes**

3-5-1. Mindfulness meditation and clinical evaluation

The method of mindfulness meditation is as a 15-minute short version^5^, based on conventional mindfulness-based stress reduction (MBSR). Participants take part in a weekly group session (approximately 30 min) of mindfulness meditation for 8 weeks, and are required to practice meditation daily for 15 min on 6 or 7 days per week. Mindfulness meditation includes body scans and controlled breathing. The participants receive instruction papers in each group session for daily home-based practice, and fill in an implementation record. Mindfulness meditation is performed in the resting or lying position, so minimally invasive and safe. In addition to regular meditation, the participants also receive instructions on meditation techniques during daily activities, such as eating meditation and walking meditation. During the period between registration and the final evaluation, the participants are prohibited from changing antiparkinsonian, antipsychotic, or antidepressant drugs. Evaluation comprises the following questionnaire and a medical examination by an investigating doctor.

3-5-2. MRI

MRI will be performed at the Wakayama Minami Radiology Clinic. T1- and T2- weighted, resting-state functional MRI are taken. The imaging time is about 30 minutes. The procedure is the same as for clinical use and the cost is covered by research funding. MRI is performed twice: during the observation period and within 14 days of the final evaluation.

**3-7. Expected benefits**

By participating in this study, there may be improvement in impulse control disorder, impulsivity or depression. In addition, it may bring unexpected health benefits, such as improved concentration. It is non-invasive and is very unlikely to have side effects.

**3-8. Expected risks and disadvantages**

Participation in this study requires group lessons each week and 15 minutes of self-practice daily at home. Participants are responsible for the cost of travel to the hospital. Drug changes are restricted during the study period. The physical burden of mindfulness meditation is negligible. For participants who have difficulty sitting for 15 minutes, it is possible to perform the meditation in a lying position or other posture.

**4. Eligibility criteria**

**4-1 Inclusion Criteria**

1. Clinically established or probable PD diagnosed by MDS clinical diagnostic criteria for Parkinson's disease.

2. 20 years or older.

3. Patients providing informed consent.

**4-2 Exclusion criteria**

1. Severe dementia or hallucinations/delusion.

2. Severe hearing loss or severe visual impairment.

3. Disturbance in consciousness.

4. Participating in other intervention trials.

5. Changed antiparkinsonian drugs within 28 days before enrollment.

6. New antipsychotics or antidepressants within 84 days before enrollment.

7. Symptomatic stroke or encephalitis within 84 days before enrollment.

8. Daily meditation or yoga.

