**5-3. Precautions**

1. Registration after the start of protocol treatment is not allowed in any case.
2. The investigators should contact the registration office if they have any questions.
3. Except in cases where consent is withdrawn, subjects will not be unregistered.
4. If incorrect registration or duplicate registration is found, the registration office is contacted immediately.
5. Intervention is started within 70 days of enrollment.

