**6. Procedure**

**6-1. Research flow**

We recruit patients with PD visiting our institute. We explain the purpose and methods of this trial, and request research participation. Participants are registered after written informed consent. After registration, participants are evaluated by cognitive test (MMSE), motor symptom evaluation (UPDRS part 3, Hoehn-Yahr), MRI, and questionnaire evaluations (BIS-11, QUIP-RS-J, HADS, PDQ-8, MAAS, NPI-Q). For cases with wear-off phenomenon, MMSE, UPDRS, and MRI should be performed in “ON” state. MRI can be skipped in difficult cases, such as for patients with claustrophobia.

Group mindfulness meditation sessions are performed once a week under the guidance of a professional clinical psychologist, including approximately 30 minutes of guidance and 15 minutes of mindfulness meditation. Mindfulness meditation includes body scans and controlled breathing. Participants are required to practice meditation daily for 15 minutes on 6 or 7 days per week. The participants are given instruction papers in each group session for daily home-based practice, and fill in an implementation record. Clinical evaluations are performed in week 2 and week 8, and MRI is conducted within 14 days after week 8 evaluation. Daily mindfulness meditation continues until the final MRI. For evaluation items and schedule, refer to “#9, Inspection items and schedule."

Concomitant prohibited drugs.

From the date of registration to the end of study, new additions and changes to antiparkinsonian drugs, antipsychotic drugs, and antidepressants are prohibited.

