**9. Inspection items and schedule**

**9-1. Inspection items and information to be reported**

- Demographics: age, gender, height, weight, medical history (duration, age at onset, etc.), medication, past history and complications, and cognitive function (MMSE).
- Motor symptoms: MDS-UPDRS, Hoehn-Yahr scale.
- Questionnaires: Impulsivity Evaluation Scale (BIS-11), Impulse Control Disorder Scale (QUIP-RS-J), Depression and Anxiety Evaluation Scale (HADS), QOL Evaluation Scale (PDQ-8), Mindfulness Evaluation Scale (MAAS) is performed after the observation period, 2 weeks and 8 weeks. If there are any caregivers, NPI- Q is also performed as an evaluation of psychiatric symptoms.
- MRI is performed twice: before the intervention and within 14 days after the end of the study.
- Evaluation of achievement rate of mindfulness meditation using implementation record (15 minutes, 6 or 7 days per week)

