**10-3. Primary outcome**

Calculate the two-sided 95% confidence interval for the BIS-11 change after 8 weeks and the *P*-value for the t-test. In addition, a summary statistic of the measured value and the amount of change at each time point is calculated.

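### Exclusion 6 screens out only newly started antipsychotics or antidepressants, so a recent dose change or stop is admitted and any drift after baseline enters the uncontrolled BIS-11 change

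*Protocol*

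**What the plan says.** Three medication-stability rules bear on this point.

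- Protocol section 4-2, exclusion 5: "Changed antiparkinsonian drugs within 28 days before enrollment".
- Protocol section 4-2, exclusion 6: "New antipsychotics or antidepressants within 84 days before enrollment". The Abstract words it the same way.
- Protocol section 6-1, repeated in the Abstract: "From the date of registration to the end of study, new additions and changes to antiparkinsonian drugs, antipsychotic drugs, and antidepressants are prohibited". Section 3-5-1 also bars changes in these three classes up to the final evaluation.

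The design in section 3-2 is "Single-center, single-arm, open-label, pilot study". Section 10-3 sets the primary analysis: "Calculate the two-sided 95% confidence interval for the BIS-11 change after 8 weeks and the" P-value of a t-test.

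Two statements govern how long a patient is on fixed medication before baseline. Section 5-3 says "Intervention is started within 70 days of enrollment", which is a maximum with no minimum. Section 9-1 says that the questionnaire assessment "is performed after the observation period, 2 weeks and 8 weeks", while the table in section 9-2 places the baseline BIS-11 in the enrolment column.

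**The concern.** The on-study rule names additions and changes separately, so the protocol treats them as different things. Exclusion 5 uses the wider notion and exclusion 6 the narrower one. Read literally, exclusion 6 admits a patient whose established antidepressant was increased, or whose antipsychotic was reduced or stopped, just before enrolment. The protocol gives no reason for asking for a settling period after a new psychotropic and none after a change or stop of an existing one.

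This matters because the primary result is a before-after change with no comparator. Stable medication is one of the few protections that such a design has against a competing explanation. HADS, PDQ-8, NPI-Q and the MRI measures, all secondary outcomes, are open to the same problem. Section 1-2 intends the results as preliminary data for phase III, so a distorted estimate could be carried forward.

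**Working it through.** **1. Coverage of the rules, side by side**

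| Drug event | Antiparkinsonian | Antipsychotic or antidepressant |
| --- | --- | --- |
| New start before enrolment | Excluded, 28 days (read as a change) | Excluded, 84 days |
| Dose change or stop before enrolment | Excluded, 28 days | **No rule** |
| Addition or change after registration | Prohibited | Prohibited |

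One cell is empty, and no other section of the protocol fills it.

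**2. Which drift counts**

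Only movement between the baseline BIS-11 and week 8 enters the primary change.

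- If baseline is taken at the end of the observation period, just before the first session, the exposed interval is 8 × 7 = 56 days. Earlier drift is already in the baseline value.
- If baseline is taken at enrolment, as the section 9-2 table allows, the interval can reach 70 + 56 = 126 days.
- With no minimum observation period, a patient may also start soon after enrolment with almost no settling time.

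**3. The plan's own figure**

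Inputs from section 10-2: expected change -10.0, SD 8.0, smallest clinically relevant change -5.0, two-sided alpha 10%, power 80%. The detectable difference is 5.

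- Normal approximation: n = (8 × (1.645 + 0.842) / 5)² = 15.8, so 16.
- Exact one-sample t-test (noncentral t): n = 18, power 81.6%.

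The stated 18 is reproduced, and this point does not dispute it.

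**4. Size of a possible shift**

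The protocol does not say how many patients would be affected or how far they would drift, so both are assumptions. If k of n = 18 patients each drift by m points in the same direction, the mean shifts by k × m / 18. The last two columns give the chance that a two-sided t-test against zero rejects when meditation has no effect, with the SD held at 8.

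| k | m | Mean shift | Share of 5.0 | Rejection at nominal 5% | Rejection at nominal 10% |
| --- | --- | --- | --- | --- | --- |
| 1 | 5 | 0.28 | 6% | 5.2% | 10.3% |
| 1 | 10 | 0.56 | 11% | 5.9% | 11.4% |
| 2 | 5 | 0.56 | 11% | 5.9% | 11.4% |
| 2 | 10 | 1.11 | 22% | 8.6% | 15.4% |
| 3 | 5 | 0.83 | 17% | 7.0% | 13.0% |
| 3 | 10 | 1.67 | 33% | 13.3% | 21.9% |

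The rejection rates are approximate, because they treat the shift as a common change in the mean.

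**5. Direction**

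Drifts need not agree. Two patients at -10 and one at +10 give (-20 + 10) / 18 = -0.56, against -1.67 if all three fell. A net upward drift would bias against meditation.

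**The case against.** The case for leaving the criterion alone has several parts.

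- **Timing.** A reader might infer that every effect of a recent psychotropic change is credited to meditation. The documents do not support that. Sections 6-1 and 9-1 fix medication from registration and place the questionnaires after an observation period, so some patients may have weeks of enforced stability before baseline. This stands as a limit on the concern. It does not remove it, because no minimum is set and the section 9-2 table lists baseline under enrolment.
- **Size.** A reader might take 33% of the clinically relevant change as the expected bias. It is the extreme corner of the table: three of 18 patients, all moving the same way, each by as much as the whole hypothesised effect of meditation. The mildest case leaves the false-rejection rate almost unchanged.
- **Mechanism.** No section says that adjusting an existing antidepressant or antipsychotic moves BIS-11 over 8 weeks. That is correct. The protocol does, however, impose a waiting period for new psychotropics and ban changes on study, so it already treats such changes as worth controlling.
- **Scope.** A reader might conclude that the stability requirement as a whole fails, or that the rules flatly contradict each other. Neither follows. The rules cover different periods, and together they handle antiparkinsonian changes, new psychotropics and all on-study changes. The gap is partial.
- **Design.** In a single-arm pilot, attribution to meditation stays limited whatever exclusion 6 says. That is true, but it is no reason to leave open a competing explanation that is cheap to close.

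**Conclusion.** The point holds in a limited form. Exclusion 6 is narrower than both exclusion 5 and the on-study rule, and patients with a recent dose change or discontinuation of an antipsychotic or antidepressant are eligible. Drift that continues after the baseline BIS-11 would be mixed into the primary change, and nothing in the design separates it.

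The size cannot be derived from the documents. On the stated assumptions (18 analysed, one to three affected, 5 to 10 points each, same direction) the mean shifts by about 0.3 to 1.7 points, and by less if directions differ. The effect is probably modest unless several such patients enrol. A reader might also infer that the 84-day period for new drugs should simply be extended to dose changes. The documents give no basis for that, since they use 28 days for changes in another class. The ambition here is to close a gap, not to set the window.

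**What to change.** - **Criterion.** In section 4-2 and the Abstract, reconcile exclusion 6 with exclusion 5 and with the on-study prohibition of "new additions and changes to antiparkinsonian drugs, antipsychotic drugs, and antidepressants are prohibited". The pre-enrolment requirement should also cover changes and discontinuations of antipsychotics and antidepressants, over a window that the sponsor chooses and justifies.
- **Patients already enrolled.** Record the date of the last antipsychotic or antidepressant change. Section 9-1 already collects medication, so this adds one date. Repeat the 8-week BIS-11 analysis without patients whose last change falls inside the chosen window. If an SAP exists, this sensitivity analysis can be placed there.

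The cost is a few words in two places, one extra date and one repeat analysis. Slightly more patients would fail screening, but section 10-2 counts about 300 patients a year for 20 places. Omitting patients from the sensitivity analysis reduces its precision, so it should be read alongside the primary result and not in place of it.
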